#### Mediating variables

Expected side effect intensity and expected coping with side effects are assessed with a modified version of the GASE [34] before (T1-pre) and after the intervention (T1-post). Patients indicate the expected intensity and coping for each of the 7 symptoms (0 ‘*not at all*’ to 10 ‘*very much*’).

#### Baseline variables

Gender, age, education, employment, psychological distress [27], the affected gastrointestinal area, physical and psychological co-morbidities are assessed using self-report. Tumor staging, aim of treatment (neoadjuvant, adjuvant, palliative etc.), and the chemotherapeutic regime are obtained from medical records. Information coping styles are assessed with two items (“To which degree do you wish to be informed about the chemotherapy?”, “How strongly do you feel the need to inform yourself about potential side effects?”), both rated on a scale of 0 (*not at all*) to 10 (*very much*).

#### Manipulation check, evaluation of the nocebo-education, process variables

Comprehension of the nocebo effect information is reviewed by asking patients in the nocebo group to describe the nocebo effect. Perceived relevance of the nocebo-education and the control intervention is assessed at T1-post. Expected efficacy of chemotherapy includes four items that assess to which degree the patient anticipates the treatment will 1) help them recover, 2) shrink the tumor, 3) improve their quality-of-life and 4) prolong their life. Each item ranges from 0 (*not at all*) to 10 (*very much*). Progression of cancer is assessed from medical records during the study period.

### Sample size calculation

In a pilot study which aimed to validate the nocebo-education session, we found a moderate to large effect (*Cohen’s d* = 0.50–0.65) when comparing post-session side effect expectations between participants who were educated vs. those who were not educated. Since no prior study has been conducted to examine the effect of a nocebo education on side effects, we used the aforementioned effect size of side effect expectations as a proxy for actual side effects. Hence, when conducting an independent *t*-test, given an effect size of *d* = 0.60, the desired power of 80%, and an alpha-error of 0.05 (two-tailed testing), we obtained a required sample size of *N* = 45 per group for this exploratory clinical study. When accounting for a dropout rate of 10%, a total sample of *N* = 100 is needed to investigate potential group differences with adequate power for our primary outcome burden of side effects.

### Data management

After data entry, 10% of the electronic data is checked for correspondence with the original paper data. Plausibility checks (e.g. for item range and scale ranges) are conducted.

### Statistical methods

All outcome analyses will be conducted for the intention-to-treat sample. Missing values will be imputed using the expectation-maximization algorithm. We will conduct ANCOVA for the primary outcomes number and intensity of side effects, and for the secondary outcomes coping with side effects, tendency to misattribute symptoms, compliance intention, attitude towards chemotherapy, and medical toxicity at both time points (10 days and 12 weeks) with adjustments for the stratum distress and for cancer staging. Logistic regression will be conducted for the secondary outcome co-medication to treat side effects with the same set of covariates. The T1-pre to T1-post changes in expected side effects and expected coping with side effects will be examined as mediators of the effect of group on the outcomes. Exploratory analyses will be conducted to compare the expected efficacy of the chemotherapy between groups using independent t-tests.

Moderate analyses will be carried out by including the group x information coping style interaction in the ANCOVA. Sensitivity analyses will be conducted under exclusion of (1) patients of the nocebo-education group who either indicated to not have heard about the nocebo effect or who gave a wrong description and (2) patients with tumor progression.

No interim analyses will be conducted.

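### Single EM imputation analysed as observed ignores imputation uncertainty: at 10% dropout, type I error is about 7–8% if treatment group is in the EM model, and the effect is diluted if it is not

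*Protocol article*

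**What the plan says.** All of this is in the Protocol article.

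- Statistical methods, analysis set: "All outcome analyses will be conducted for the intention-to-treat sample".
- Statistical methods, missing data: "Missing values will be imputed using the expectation-maximization algorithm". No multiple imputation, bootstrap, variance correction or likelihood-based model is mentioned, and the variables that enter the EM model are not listed.
- Statistical methods, model: "We will conduct ANCOVA for the primary outcomes number and intensity of side effects", at both follow-up times, "with adjustments for the stratum distress and for cancer staging". The continuous secondary outcomes get the same model, and the yes/no co-medication item gets logistic regression with the same covariates.
- Statistical methods, sensitivity: "Sensitivity analyses will be conducted under exclusion of (1) patients of the nocebo-education group" who fail the knowledge check, and (2) patients whose tumour progresses. Neither analysis concerns missing data.
- Sample size calculation: a two-sided 5% test and 80% power at d = 0.60 need 45 per group. The total of 100 follows from the step that begins "When accounting for a dropout rate of 10" per cent. This is the only missingness figure in the document.

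**The concern.** The EM algorithm estimates means and covariances. Used as an imputation method, it normally supplies one conditional mean for each missing value. Patients filled in this way lie exactly on the fitted surface, but a later ANCOVA counts each of them as a full, independent observation. They add degrees of freedom and no residual scatter, and nothing in the standard error reflects that their values are estimates.

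What follows depends on whether treatment group is one of the EM variables. If it is, the treatment estimate is sound but its standard error is too small, so p-values and intervals are too optimistic. If it is not, filled values are pulled towards a mean common to both arms, and the treatment difference is pulled towards zero. Neither planned sensitivity analysis would reveal the problem.

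The 12-week side-effect questionnaires are collected by mail from a population that includes first-line palliative patients, so some missing outcomes are foreseeable.

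**Working it through.** **The plan's own figure.** For d = 0.60, two-sided alpha 0.05 and an independent t-test, the noncentral t distribution gives 79.5% power at 44 per group and 80.4% at 45. So n = 45 per group, and 90 / 0.9 = 100. The sample size reproduces, and 10% is the planning value for missing outcomes.

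**Analytic check, group in the EM model.** Inputs: N = 100, n_obs = 90 (10% missing), four ANCOVA parameters (intercept, group, distress, stage as one term), and no information from other variables about the missing values. Filled values have zero residual, so the residual sum of squares is that of the observed patients, but it is divided by N − 4 and the sample is treated as size N:

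reported SE / true SE = √[(n_obs − 4)/(N − 4)] × √(n_obs/N)

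- 10% missing: √(86/96) × √0.90 = 0.946 × 0.949 = 0.898, so the SE is 10% too small. The critical value 1.985 (96 df) acts as 1.985 × 0.898 = 1.78. The true two-sided error is 7.5% (normal reference) to 7.8% (t reference).
- 20% missing (assumed): √(76/96) × √0.80 = 0.796, giving 11.4–11.8%.

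**Simulation of the 12-week outcome.** The documents do not give these settings, so they are assumptions: 50 per arm; normal outcomes; a binary distress stratum and four-level stage; an expectation covariate; a shared T2–T3 variance component of 0.5 plus a small expectation effect (residual correlation (0.5 + 0.09)/1.09 = 0.54); the same treatment effect at T2 and T3; data missing completely at random, with T2 missing at half the T3 rate. The ANCOVA is on group, distress and stage. Each cell has 2,000 to 6,000 replicates.

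| Method | Type I error, 10% missing | Type I error, 20% missing | 95% CI coverage at d = 0.6, 10% / 20% missing |
|---|---|---|---|
| EM fill, group in model | 6.8% | 10.2% | 92.9% / 88.5% |
| EM fill, group left out | 4.9% | 4.6% | 94.5% / 91.8% |
| Available cases | 4.8% | 4.8% | 95.1% / 94.5% |
| Multiple imputation, 20 sets, Rubin's rules | 4.7% | 4.3% | 95.5% / 95.3% |

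The Monte Carlo standard error of the type I errors is about 0.3 points at 10% missing and 0.4 to 0.6 points at 20%.

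- *Group in the model.* The mean reported SE divided by the empirical SD under the null is 0.92 at 10% and 0.83 at 20% missing. A second simulation setting gave 7.4–7.7% type I error at 10%. With the analytic case, the range is 6.8–7.8% at 10% and 10.2–11.8% at 20%.
- *Group left out.* The reported SE matches the empirical SD under the null (ratio 1.00), because the estimate itself varies less. The cost is bias. At d = 0.6, the mean estimate relative to available cases is 0.937/1.013 = 0.925, about 0.93, at 10% missing and 0.858/1.009 = 0.85 at 20%. Power was not lower than with available cases (80.9% against 79.9% at 10%), so the harm here is a diluted estimate rather than lost power.

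Available-case ANCOVA and multiple imputation stay close to 5% on the same data, so the distortion comes from the single fill and not from the missing data as such.

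**The case against.** The article names only the algorithm. It does not say that values are filled once, or with a conditional mean, and a condensed article may leave the variable list to an analysis plan not shown here. The trial calls itself exploratory, non-responders get a reminder call, and at the planned dropout the distortion is modest. The point about exploratory status and modest size stands and limits the consequence. The defence that this is mere missing detail does not stand: a method is stated, one completed data set is its ordinary meaning, and no correction is attached to it. The trial also describes itself as a superiority trial, names primary outcomes and is sized for a two-sided 5% test.

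A reader might infer more than the documents support:

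- *That type I error exceeds 5% in any case.* It does so if group is in the EM model or EM is run by arm. With group left out it stays near 5%.
- *That 20% or more missing data is planned.* The article plans for 10%; 20% is a scenario.
- *That every p-value and interval is affected to this degree.* The simulation covers one continuous outcome at 12 weeks. Loss may be smaller at 10 days, and clinician-rated toxicity is recorded at each cycle rather than by mail.
- *That logistic regression will receive fractional co-medication values.* This follows only if a normal-model EM fill is left unrounded, which the article does not say.
- *That symptom scores will be imputed after death.* The article is silent on this, and it is a separate question.

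**Conclusion.** The concern holds in conditional form. Followed as written and read in the ordinary way, the plan produces either standard errors that are too small or a diluted treatment effect, depending on an unstated choice. The sizes are those in the working: at 10% dropout, a type I error of about 7–8% with an SE 8–10% too small, or an effect at about 0.93 of its size; at an assumed 20% missing, about 10–12% or about 0.85.

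These figures rest on normal outcomes, a T2–T3 correlation near 0.5, data missing completely at random and, for the attenuation, an equal effect at both follow-up times. The direction in each case follows from the method; the exact size would move with these assumptions.

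**What to change.** Replace the EM sentence with multiple imputation: at least 20 data sets; treatment group, both time points, distress stratum and stage in the imputation model; and a logistic model for the yes/no co-medication item. Run the planned ANCOVA or logistic regression in each data set and pool with Rubin's rules. For the continuous outcomes, a likelihood-based repeated-measures model that uses all observed data without imputing outcomes is an acceptable alternative.

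The cost is changed wording and a little more analysis work, with no new data. Confidence intervals become slightly wider, and correctly so. In the simulation, power at d = 0.6 under multiple imputation was about 80% at 10% missing, the planned level, and about 75% at 20%.

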In clinical practice, patients are briefed about the treatment including potential risks in the informed consent. Although a great achievement towards patient autonomy, standard informed consent procedures may facilitate negative expectations which can, in turn, cause nocebo effects [18]. As reported in a meta-analysis, negative pre-treatment expectations predict the occurrence of actual side effects [19]. The strongest associations between symptom expectation and symptom occurrence were found for pain, fatigue, and nausea [19]. Moreover, negative treatment expectations prior to chemotherapy are high. In a study by Hofman and colleagues [20], most of the cancer patients expected that they would develop severe or long-lasting side effects such as fatigue (90.6%) and nausea (78%). In summary, optimizing informed consent procedures may be an essential module in the prevention of nocebo effects during chemotherapy.

By acknowledging the ethical and legal necessity of informed consent on the one side and the importance to minimize risks on the other, Barsky and colleagues [21] suggested educating patients about the nocebo effect. When aware of the existence of expectation-induced nocebo effects, patients’ risk of misattributing unspecific symptoms to the treatment may be lower and they may be less vigilant to bodily signals, which again, may decrease the number and intensity of symptoms [22]. First evidence has shown that informing participants about the nocebo effect led to a reduction of symptoms that were allegedly caused by wind turbines [23]. Despite the high relevance of preventing nocebo effects during routine chemotherapy treatments, no comparable research has yet been conducted in the clinical context.

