### Study sample

Patients with newly diagnosed cancer of the gastrointestinal tract, including the esophagus, stomach, colon, rectum, anus, pancreas, gallbladder and bile duct who are indicated for chemotherapy are eligible for this study. Chemotherapy can be given in the adjuvant, neoadjuvant, or first-line palliative setting, and is administered as a mono chemotherapy or combination-chemotherapy, with or without vascular endothelial growth factor (VEGF)-antibody. To enroll, patients must be at least 18 years old, have no difficulties understanding German, and be able to give informed consent. Exclusion criteria include the following: any chemotherapy before trial inclusion, limited capability of self-care (Eastern Co-operative Oncology Group (ECOG) ≥ 3 [26]), severe comorbid psychological disorder (schizophrenia, substance abuse, severe depression or severe anxiety disorder), concurrent psychotherapeutic or psychopharmacological treatments, life-threatening comorbid medical condition, diagnosis of chronic skin disease, dyspnea, or chronic lung diseases due to its interference with chemotherapy side effects, indication for epidermal growth factor receptor (EGFR)-antibody treatment since it may cause acne-like rash. Since prior research has found that the link between negative treatment expectations and side effects was more pronounced among patients who had chemotherapy experience [19], we excluded patients with prior chemotherapy experience, including having received the first dose before enrolment, to achieve an increased homogeneity of the sample.

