### Measures

#### Primary outcomes

The mean group difference in number and intensity of patient-reported side effects at 10 days and 12 weeks after the initial chemotherapy session are defined as primary outcomes. Based on the Generic Assessment of Side Effects (GASE) [31], we chose four side effects specific to the chemotherapy, i.e., nausea, vomiting, diarrhea, and fatigue [32, 33]. Three unspecific symptoms, i.e., headache, shortness of breath, and rash, were defined as side effects that were very unlikely to occur in pharmacodynamic relation to the chemotherapy. They were chosen as a result of discussions among the research staff oncologists. A global item assesses the overall intensity of side effects in the last 7 days. The original GASE ranged from 0 to 3; to optimize outcome sensitivity in this exploratory trial, we increased the item range from 0 (*not at all*) to 10 (*very much*). Numbers of side effects are computed by adding up the number of present symptoms (≥ 1).

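### The primary ANCOVA leaves out three baseline variables the trial already collects; the cost is precision, not bias

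*Protocol article*

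**What the plan says.** Under Statistical methods the article commits to a model: "We will conduct ANCOVA for the primary outcomes number and intensity of side effects", at both time points, with the distress stratum and cancer staging as the only adjustment variables. Under Primary outcomes, "Numbers of side effects are computed by adding up the number of present symptoms", where present means a rating of at least 1 on the 0 to 10 scale. Table 1 schedules GASE number and intensity at T2 and T3 only.

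The trial records other baseline information:

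- **Expected side effects (GASE-Expect):** taken at T1-pre and T1-post (Table 1; Mediating variables). They enter the analysis only through the T1-pre to T1-post change, which is examined as a mediator. The Background says that "negative pre-treatment expectations predict the occurrence of actual side effects".
- **CTC toxicity:** scheduled at T1-pre, T2 and T3 (Table 1). The T1-pre value has no stated use.
- **Regimen:** the treatment "is administered as a mono chemotherapy or combination-chemotherapy" (Study sample), and tumor staging, treatment aim "and the chemotherapeutic regime are obtained from medical records" (Baseline variables).

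Randomization is stratified by distress alone (Randomization and blinding).

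**The concern.** Side-effect ratings a few days or weeks into chemotherapy should depend on what the patient already felt, on what is being infused and, by the protocol's own argument, on what the patient expected. The model contains none of these directly. Fatigue, nausea or headache that predates chemotherapy adds to the symptom count, and no baseline rating exists to account for it. Regimen is mixed by design and is handled neither by stratification nor by adjustment.

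At stake is the sharpness of the primary comparison. Variance that recorded variables could explain stays in the error term, and a chance difference between arms in those variables is left uncorrected. This matters more here because the Discussion concedes that the sample is small and that the effect size was borrowed from a proxy outcome, so the true effect may be below 0.60.

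**Working it through.** **Inputs.** From Sample size calculation: two-sided alpha 0.05, "the desired power of 80" per cent, "given an effect size of *d* = 0.60", independent t-test, 45 per group, 10% dropout, N = 100. Assumed, because the document gives no figure: the share R² of the variance remaining after distress and staging that the added covariates explain, taken as 10%, 20% and 30%.

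**1. The plan's own figure.** The exact two-sided t-test at d = 0.60 needs 44.59 per arm, so 45. Power at 45 per arm is 80.4%. Dropout: 90 / 0.90 = 100. The stated sample size reproduces with no covariate at all.

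**2. Gain from the added covariates.** ANCOVA shrinks the residual SD by √(1 − R²), so the effective effect size is 0.60 / √(1 − R²).

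| R² (assumed) | Effective d | Power, 45 per arm | Smallest effect detectable at 80% power |
|---|---|---|---|
| 0 | 0.600 | 80.4% | 0.597 SD |
| 10% | 0.632 | 84.3% | 0.597 × √0.90 = 0.567 SD |
| 20% | 0.671 | 88.2% | 0.597 × √0.80 = 0.534 SD |
| 30% | 0.717 | 92.0% | 0.597 × √0.70 = 0.500 SD |

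Cutting the error degrees of freedom from 88 to 85 for three extra covariates changes each power by less than 0.1 percentage point. The reference row credits nothing to distress and staging, as the protocol's own calculation does.

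**3. If the true effect is smaller.** At d = 0.40 with 45 per arm, power is 46.7% without the added covariates. It is 50.7%, 55.5% and 61.1% at R² of 10%, 20% and 30%.

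**4. Chance imbalance.** The standardised arm difference in any unstratified baseline variable has SD √(2/45) = 0.21. It exceeds 0.2 SD in 34% of trials and 0.3 SD in 15%. For a regimen feature present in half the patients (assumed), the SD of the difference in proportions is √(2 × 0.25 / 45) = 0.105, so the 95% range is ±1.96 × 0.105 = ±21 percentage points. If that feature shifts intensity by 0.8 SD (assumed), the treatment estimate moves by up to 0.8 × 0.207 = 0.165 SD at the edge of that range.

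**5. Is there bias?** In 40,000 simulated trials per setting, with 45 per arm and a covariate correlated 0.3, 0.5 or 0.7 with the outcome, the unadjusted test rejected a true null in 4.9% to 5.0% of trials. At a true effect of 0.60 the mean unadjusted estimate was 0.60. The SD of the estimate was 0.21 unadjusted; with ANCOVA it was 0.203, 0.183 and 0.151. The only change is in precision.

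**The case against.** The strongest reply is that the stated model is valid. The trial is randomized and stratified by distress, and the analysis adjusts for the stratum and one prognostic factor. It holds its error rate and meets its planned power without the extra covariates. That stands. A reader might infer that regimen differences or pre-existing symptoms confound the comparison, or that imbalance will be mistaken for a nocebo effect. The document does not support this: chance imbalance is random with respect to arm and is already in the standard error. The shift of up to 0.165 SD in step 4 is part of that error, not an addition to it.

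The assumed 10% to 30% may also be generous. Study sample reports that the link between expectations and side effects was more pronounced in patients with chemotherapy experience, and those patients are excluded, so GASE-Expect may predict less well here than the Background suggests. T1-pre CTC may vary little in chemotherapy-naive outpatients. Staging may partly stand in for treatment setting. These points argue for the lower end of the range and for checking CTC before using it.

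The exclusions for chronic skin disease, dyspnea and chronic lung disease limit pre-existing rash and shortness of breath. They do not cover fatigue, nausea, vomiting, diarrhea or headache, which are five of the seven symptoms.

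Adjusting for T1-pre expectations does not conflict with the mediation analysis. The mediator is the change after T1-pre, and the T1-pre value precedes the intervention.

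Finally, the covariate list is stated in the article. This is therefore a comment on a choice made, not on detail left to an analysis plan that is not shown.

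**Conclusion.** The point holds as a worthwhile, nearly free improvement to a stated choice. It is not an error or a contradiction. The primary outcome has no baseline, and the model omits three recorded variables that are likely to be prognostic, one of which the protocol itself calls predictive. The likely gain is from 80.4% power to about 84% at 10% of residual variance explained, and to 88% or 92% at 20% or 30%. The size rests wholly on those assumed shares. Type I error, unbiasedness and N = 100 are unaffected.

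**What to change.** Before analysis, pre-specify the primary ANCOVA covariates as distress stratum, cancer staging, regimen class (mono versus combination) and mean T1-pre GASE-Expect. Add worst T1-pre CTC grade if it shows enough spread when inspected blind to arm, with that rule written down beforehand.

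Do not try to repair the missing baseline by adding symptom ratings at T1-pre partway through. Enrolment began in September 2015, so only later patients would have them, and using a covariate where available does not define a single model. State the absence of a baseline GASE rating as a limitation; the Discussion does not currently list it.

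The cost is a change to the analysis wording and about three degrees of freedom. It needs no new data and places no further burden on patients.

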## Methods

### Study design

The RENNO trial (German Acronym for “**R**eduzierung des subjektiven **E**rlebens von **N**ebenwirkungen während der Chemotherapie durch Aufklärung über den **No**cebo-Effekt”) is a randomized-controlled, single-site superiority trial with two parallel arms and a primary endpoint of patient-reported number and intensity of side effects at 10 days and 12 weeks after the first chemotherapy session. Patients with newly diagnosed gastrointestinal cancers scheduled for chemotherapy are block-randomized 1:1 to a nocebo-education group or an attention control group entailing a quality-of-life interview.

The intervention takes place < 24 h before chemotherapy commences or during the administration of the first dose. Measurements are taken before (T1-pre), and after the intervention (T1-post), and 10 days (T2) and 12 weeks (T3) after the initial chemotherapy (Table 1).

**Table 1 Tab1:** Schedule for enrolment, interventions and assessments

Time points	Study period				
	Allocation	Post-allocation			
	t_1pre_	t_1_	t_1post_	t_2_	t_3_
ENROLMENT					
Eligibility screen^a^	✓				
Informed consent	✓				
Randomized assignment	✓				
INTERVENTIONS					
Nocebo-education group		✓			
Attention control group		✓			
ASSESSMENTS					
Baseline variables					
Demographic and medical characteristics	✓				
Distress Thermometer	✓				
Information coping style	✓		✓		
Outcome variables					
Side effect number and intensity (GASE)^b^				✓	✓
Coping with side effects (GASE-Coping)				✓	✓
Misattribution of symptoms (GASE-Attribution)				✓	✓
Co-medication to treat side effects (yes/no)				✓	✓
Compliance intention	✓		✓	✓	✓
Attitude towards the chemotherapy	✓		✓	✓	✓
Severity of toxicity (CTC)^c^	✓			✓	✓
Further variables					
Expected side effects (GASE-Expect)	✓		✓		
Expected coping with side effects (GASE-Coping Expect)	✓		✓		
Expected efficacy of chemotherapy			✓		
Relevance of the conversation			✓		
Knowledge about the nocebo effect^d^			✓	✓	✓
Disease progression				✓	✓

*Note.* The time points T1-pre and T1-post refer to the intervention whereas the T2 and T3 refer to the chemotherapy (10 days and 12 weeks after the initial chemotherapy). *GASE* Generic Assessment of Side Effects, *CTC* Common Toxicity Criteria

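### The ANCOVAs for compliance intention and attitude leave out the pre-intervention value of the same items, which is collected, and so give up precision on these secondary outcomes

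*Protocol article*

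**What the plan says.** The Statistical methods section of the protocol article plans ANCOVA at 10 days and 12 weeks for the primary outcomes and for most secondary outcomes, including compliance intention, attitude and toxicity. All of these models are fitted "with adjustments for the stratum distress and for cancer staging". The logistic regression for co-medication is then to be run "with the same set of covariates", so the list reads as complete. Change scores are not mentioned for any of these outcomes. T1-pre to T1-post change appears only for the expectation mediators.

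Table 1 (Study design) marks the rows "Compliance intention" and "Attitude towards the chemotherapy" at T1-pre, T1-post, T2 and T3. Toxicity (CTC) is marked at T1-pre, T2 and T3. The number and intensity of side effects (GASE), coping, misattribution and co-medication are marked at T2 and T3 only. According to the Secondary outcomes section, compliance intention has two items (one scored 0 to 10, one a percentage) and attitude has one item (0 to 10).

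**The concern.** When the same question is put before and after an intervention, the earlier answer is a natural predictor of the later one. For compliance intention and attitude it may well predict better than a two-level distress stratum or tumour stage. If it is left out of the model, the variance it would explain stays in the error term, and a chance difference between arms at T1-pre is only partly corrected, through whatever distress and staging happen to capture. With about 45 patients per arm after dropout, chance differences of some size are common. At stake is the precision of the treatment comparison on these two secondary outcomes.

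**Working it through.** **Inputs from the protocol article (Sample size calculation):** d = 0.60, power 80%, two-sided alpha 0.05, 45 per group, 10% dropout, 100 in total. Allocation is 1:1 (Study design).

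**Assumed:** r, the correlation between the T1-pre and follow-up values of the same item. It is taken as the partial correlation given distress and staging, because those two are already in the model. The article gives no value, so 0.1 to 0.7 is shown. d = 0.40 is added as an illustration and is not from the article. d is in units of the SD that remains after distress and staging, and each of those is counted as one degree of freedom.

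**1. The plan's own figure.** The t-test solution for d = 0.60 is 44.59, so 45 per group (power 80.4%). With dropout, 90 / 0.9 = 100. The stated sample size reproduces. It was set for the primary outcome and is not affected by this point.

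**2. Precision.** Adding the T1-pre value multiplies the residual variance by 1 − r², which is worth a factor of 1/(1 − r²) in sample size. Power comes from the noncentral t distribution with

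noncentrality = d / √(1 − r²) × √(n/2), n = 45.

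Degrees of freedom are 90 − 2 − 2 = 86 without the T1-pre value and 85 with it. For example, d = 0.60 and r = 0.5 give 0.60 / 0.866 × √22.5 = 3.29, and power 90.1%.

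| r | Residual variance removed | Sample-size equivalent | Power, d = 0.60 | Power, d = 0.40 |
|---|---|---|---|---|
| not adjusted | – | 1.00 | 80.3% | 46.7% |
| 0.1 | 1% | 1.01 | 80.7% | 47.0% |
| 0.3 | 9% | 1.10 | 83.9% | 50.3% |
| 0.5 | 25% | 1.33 | 90.1% | 58.2% |
| 0.7 | 49% | 1.96 | 97.6% | 74.8% |

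**3. Chance imbalance.** The SD of the difference in baseline means is √(2/45) = 0.21 SD. A difference of at least 0.2 SD in either direction has probability 2 × (1 − Φ(0.2/0.211)) = 0.34. The share that reaches the estimate is r × imbalance. For 0.2 SD this is 0.02, 0.06, 0.10 and 0.14 SD at r = 0.1, 0.3, 0.5 and 0.7.

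**4. Toxicity.** The Study sample section excludes "any chemotherapy before trial inclusion". The T1-pre CTC grade is therefore a pre-treatment value and probably near the floor. A covariate that hardly varies explains little, so the upper rows of the table are the relevant ones for toxicity.

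**The case against.** The planned analysis is valid. Randomization keeps the comparison unbiased on average, type I error is not inflated, and the stratification factor is in the model. One covariate set for all outcomes, with or without a baseline, is a defensible and simple choice. The trial calls itself exploratory and claims power only for its primary outcome. The Discussion says that the one- and two-item measures have not been validated. Unreliable single items, followed over 12 weeks of chemotherapy, may have a low r, and at r = 0.1 the gain is under one percentage point of power. All of this stands, and it limits the weight of the point.

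It could also be said that one sentence in a condensed article should not be read so strictly, since a fuller protocol or analysis plan may exist. That carries less weight. The article does not leave the covariates open: it names them and then refers back to them as a set. If a fuller document adds the T1-pre value, the two need to be reconciled.

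A reader might infer more than the article supports:

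- **That a baseline imbalance passes in full into the estimated effect.** Only the fraction r does.
- **That the primary result is weakened.** The GASE outcomes have no T1-pre value, so no such adjustment is possible. The same holds for coping, misattribution and co-medication.
- **That toxicity stands to gain as much as the self-report items.** Patients have had no chemotherapy at T1-pre, so little gain is expected there.

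**Conclusion.** The point holds for the two compliance-intention items and for attitude. The stated models omit a pre-intervention measure of the same outcome that the trial already collects. This is a loss of efficiency, not an error that threatens validity, and it concerns secondary outcomes only.

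Its size depends on a correlation that the article does not give: from almost nothing at r = 0.1, through the equivalent of one third more patients at r = 0.5, to nearly twice as many at r = 0.7. The upper end has no support in the article and should be read as a bound on the illustration. The d = 0.60 behind the 80.3% is the protocol's proxy for side effects, not an estimate for attitude or intention. The change is worth making because it costs almost nothing even if r proves low.

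**What to change.** In Statistical methods, extend the ANCOVA sentence. For each compliance-intention item and for attitude, the model also includes the T1-pre value of the same item, alongside distress stratum and cancer staging. For toxicity, the T1-pre CTC grade is added only if it varies between patients. The T1-post value should not take this role, since it is measured after the intervention. The models for the primary outcomes, coping, misattribution and co-medication stay as they are.

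The cost is one sentence and one degree of freedom per model. No data are added, and the sample size is unchanged. The change should be fixed before outcomes are seen by arm, so that there is no later choice between adjusted and unadjusted results.
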